#### Control group

This group receives the usual standard treatment (diabetic control and management) given to patients with T2DM. Although the controls have access to the Internet, they receive neither website log-in information, nor any reinforcement via e-mail or SMS.

#### e-Intervention group

This group receives an intensive dietary intervention through the study website, personalised according to the participants' SOC, in addition to the usual standard treatment at the outpatient clinics.

### Intervention programme

#### Dietary module

Twelve dietary lesson plans are developed for the intervention based on the Nutrition Recommendations and Interventions for Diabetes by American Diabetes Association [22], Malaysian Clinical Practice Guidelines for Type 2 Diabetes Mellitus [23] and Malaysian Medical Nutrition Therapy Guidelines for Type 2 Diabetes [24]. The intervention's structure and materials are developed using TTM's Stages of Change construct [17] (Table 2). The content of each lesson plan is studied for its relevance to the local community and fine-tuned to suit local context.

**Table 2 T2:** Five Stages of Change, its characteristics and relevant strategies (Kendra C 2010)

Stage	Characteristics	Strategies
**Pre-contemplation**	• Not intending to change in the next 6 months. •In denial or ignorant of the problem.	•Encourage the patient to self-analyse and rethink his/her behaviour. •Explain the risks of current behaviour.

**Contemplation**	•Intending to change in the next 6 months. •Having conflicting emotion.	•Weigh the pros and cons of changing behaviour. •Address barriers and encourage confidence.

**Preparation**	•Planning to change in the next 30 days and have made a previous attempt to improve. •Experimenting and collecting information about change.	•Prepare an action plan or goal. •Motivate the patient to change.

**Action**	•Taking actions towards achieving the goal for at least the last 6 months.	•Encourage the patient to seek social support and motivate him/her to sustain the behaviour. •Reward for the success.

**Maintenance**	•New behaviour is sustained for at least 6 months.	•Strategies to cope with temptation. •Reward for the success.

### Website design

Suitable features to be highlighted in the website are discussed by a research panel comprising of nutritionist, behavioural psychologists, endocrinologist, public health expert, and a web master. Figure 3 outlines the structure of the study website, *my*DIDeA *(Dietary Intervention for Type 2 Diabetes Patients: An e-Approach)*.

**Figure 3 F3:**
[figure not shown]
**The website structure**.

*my*DIDeA will be tailored according to the participants' SOC. Each lesson plan has five Likert scale items (strongly agree = 5 to strongly disagree = 1) and participants are assigned to recommendations based on the score obtained. The recommendations are aimed to address the barriers and motivate the participants according to the lesson plan and stage. Relevant photographs and illustrations are added to enhance the understandability of the lesson plans. Factsheets and statistics on diabetes, links to existing diabetes resources and an example of ideal health profile also are included.

The participants are briefed on *my*DIDeA, and are provided with unique username and password via e-mail or SMS after the randomisation. Log-in reminders are sent to their e-mail each time *my*DIDeA is updated with new lesson plan. The participants are also encouraged to send their queries to the study nutritionist via the website.

### Outcome assessments

All assessments (Table 3) are conducted at the clinical settings by trained enumerators.

**Table 3 T3:** Assesments that will be carried out in the study

Outcome	Measure	Instrument
Primary	Nutrition KAB related to T2DM	Dietary Knowledge, Attitude and Behaviour Questionnaire*

Secondary	Dietary practices Height Weight and body composition Waist circumference Systolic and diastolic blood pressure FBS, HbA1c and lipid profile	Semi-Food Frequency Questionnaire* 24-hour dietary recall Supplement intake Cooking method Eating out habit Body meter Four-point digital weighing scale Non-elastic measuring tape Automatic blood pressure monitor Medical record

Others/Covariates	Socio-demographic characteristics Medical history Physical activity Stages of change	Pretested questionnaire International Physical Activity Questionnaire Stages of Change Questionnaire*

*validated instrument

#### Primary outcomes

The primary outcome is assessed using a validated interviewer-administered dietary KAB questionnaire in English and Bahasa Malaysia.

#### Secondary outcomes

A semi-food frequency questionnaire (SFFQ) is used to record the subjects' dietary intake, while two days 24-hour dietary recall is used to analyse the nutrient intake [25]. Besides SFFQ and 24-hour dietary recall, consumption of supplements, cooking techniques and eating out habit for the past one month are also recorded. Anthropometric measurements (body mass index, waist circumference and percentage of body fat) and blood pressure are taken during the interview sessions. The results of participants' blood biomarkers are obtained from their medical record.

#### Process evaluation

Adherence to the intervention is assessed by the number of log-ins and duration spent in the website. Besides, the participants' satisfaction of the intervention is assessed by self-administered questionnaire at post-intervention.

#### Other measurements

The socio-demographic characteristics, medical history, and smoking and drinking habits are recorded in a structured questionnaire. International Physical Activity Questionnaire (IPAQ) is used to determine the level of physical activity of the participants [26].

### Blinding

It is not possible to blind study nutritionist, webmaster and the participants. The enumerators trained to collect the data, however, are blinded during the data collection.

### Statistical analysis

Axxya Systems Nutritionist Pro™ Diet Analysis is used to analyze the nutrient intakes and all statistical analyses are performed with IBM^® ^SPSS^® ^Statistics 17.0. Independent *t*-test or equivalent is used to determine differences between the study groups for continuous variables, while χ^2 ^or equivalent is used to determine the association between categorical variables. As this is a prospective RCT involving repeated measures, the ANOVA repeated measures model is applied to observe significant differences within the study groups. The evaluation of the intervention is based on an intention-to-treat analysis, with the *p *value 0.05 was taken as the level of significance.

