## Methods/Design

### Study design

This is a two-armed matched-design randomized controlled trial (RCT) scheduled for 12 months (Figure 1). The study is designed according to the recommendations of the CONSORT statement for randomised trials of non-pharmacologic treatment [19].

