### Study sample

#### Sample size and power calculation

The sample size calculation is based on a difference in fat and fibre-related behaviour score as reported by a previous computer assisted dietary intervention study in type 2 diabetics [20]. Using a reduction in the mean behaviour score from 1.93 ± 0.5 (baseline) to 1.69 ± 0.4 (post intervention), the GPower software [21] calculated that 31 patients are needed in each group to detect this difference with a two-sided alpha of 0.05, a power of 80%. Based on 30% attrition rate for one year, a minimum of 41 participants are required in each group.

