### Randomisation and treatment allocation

Eligible diabetic patients who have consented to participate are matched for age, sex and ethnicity, and randomised to either e-intervention or control group.

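### Patients are matched on age, sex and ethnicity before randomisation, but the between-group tests use none of these factors; if the factors predict KAB, the comparison is conservative and loses power.

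*Protocol article*

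**What the plan says.** The Study design section of the Protocol article states: "This is a two-armed matched-design randomized controlled trial (RCT) scheduled for 12 months". Under Randomisation and treatment allocation, eligible patients "are matched for age, sex and ethnicity, and randomised to either e-intervention or control group". The article does not say whether this means individual pairs or frequency matching.

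The Statistical analysis section assigns the between-group comparison of continuous outcomes to an independent t-test, which "or equivalent is used to determine differences between the study groups for continuous variables". Categorical variables get chi-square or an equivalent. Repeated-measures ANOVA has a different role: "the ANOVA repeated measures model is applied to observe significant differences within the study groups". That section names no pair or stratum term, no paired test and no adjustment for the matching factors.

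**The concern.** Matching on age, sex and ethnicity makes the arms alike on those factors. If the factors predict KAB, the true variance of the difference between arms is smaller than it would be for two unrelated samples. The independent t-test still computes the variance as if the samples were unrelated. The matching improves the estimate, but the standard error gives no credit for it: confidence intervals are wider than they need be and p-values are too large. Chi-square has the same defect for categorical outcomes.

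What is at stake is power on the primary outcome, in a trial with little to spare.

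**Working it through.** **Inputs from the article (Sample size and power calculation).** "Using a reduction in the mean behaviour score from 1.93 ± 0.5 (baseline) to 1.69 ± 0.4 (post intervention"; "31 patients are needed in each group to detect this difference with a two-sided alpha of 0.05, a power of 80" per cent; "Based on 30% attrition rate for one year, a minimum of 41 participants are required in each group".

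- Difference: 1.93 − 1.69 = 0.24.
- Pooled SD: √[(0.5² + 0.4²)/2] = 0.453.
- d = 0.24/0.453 = 0.53.

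**The article's own figure.** A paired calculation with an assumed correlation of 0.5 gives an SD of the difference of √(0.25 + 0.16 − 2 × 0.5 × 0.5 × 0.4) = 0.458 and 31 pairs (power 80.6%), which reproduces 31. The independent t-test on the same inputs needs 57 per group. The figure of 41 is 31 × 1.3 = 40.3, rounded up. How 31 and 41 were derived is a separate matter. Here it shows only that the named test starts well below 80% power.

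**Completers.** 41 × 0.7 = 28.7, so about 29 per arm. The independent t-test with 29 per arm and d = 0.53 has 51% power. If dropout is independent within pairs, 0.7 × 0.7 = 49% of pairs stay complete, which is 20 of 41.

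**Assumption.** Let R² be the share of KAB variance explained by age, sex and ethnicity. The article gives no value, so 0 to 0.3 is shown.

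**Unadjusted test, by formula.** Both arms start with the same factor values. After random loss of 30%, each arm's factor mean varies around the common mean with variance (R²σ²/28.7) × 0.3. The residual part contributes (1 − R²)σ²/28.7. Over both arms the true variance is

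(2σ²/28.7) × (1 − R² + 0.3R²) = (2σ²/28.7) × (1 − 0.7R²).

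The t-test reports about 2σ²/28.7, so its standard error is too large by a factor of 1/√(1 − 0.7R²). The actual type I error is the two-sided tail area beyond 2.003 (the 5% critical value on 56 df) times that factor.

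**Adjusted model, by formula.** The standardised effect becomes 0.53/√(1 − R²). The noncentrality is that value × √(28.7/2) = that value × 3.788. Power is taken on about 52 df.

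| R² | SE too large by | Unadjusted type I | Adjusted effect | Noncentrality | Adjusted power |
|---|---|---|---|---|---|
| 0 | 0% | 5.0% | 0.530 | 2.01 | 50% |
| 0.1 | 4% | 4.2% | 0.559 | 2.12 | 55% |
| 0.2 | 8% | 3.5% | 0.593 | 2.25 | 60% |
| 0.3 | 13% | 2.8% | 0.634 | 2.40 | 65% |

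**Simulation of the same setting.** 41 matched pairs, 30% independent individual dropout and d = 0.53; t-test against a linear model with the three factors.

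| R² | Power, unadjusted v adjusted | Unadjusted type I |
|---|---|---|
| 0 | 50% v 49% | 4.8% |
| 0.1 | 51% v 54% | 4.2% |
| 0.2 | 51% v 59% | 3.7% |
| 0.3 | 51% v 64% | 2.8% |

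The adjusted model's type I error is about 5% throughout. The 4.8% at R² = 0 is simulation error around 5%. A repeat with 8,000 trials per setting agreed to within about one point. Adjusted power falls about a point short of the formula because some chance imbalance in the factors remains after dropout.

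**A plain paired t-test.** On 20 complete pairs it has 36%, 39%, 43% and 47% power at within-pair correlations of 0, 0.1, 0.2 and 0.3, which is worse than the 51% of the independent test.

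**The case against.** Several points on the other side carry weight.

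- **The loss is conditional.** It arises only if age, sex and ethnicity predict KAB. Patients with a baseline KAB score above 50% are excluded, and this cut may weaken any such association. This stands: the gain is nil at R² = 0 and about three points at 0.1.
- **Validity is not harmed.** The type I error stays at or below 5%. This stands. A reader might infer that the trial's p-values cannot be trusted or that a positive result would be unsafe; the documents do not support that. Nor do they support saying that the matching brings no precision at all: the estimate keeps whatever balance it provides, and only the standard error fails to reflect it.
- **Complete-pair figures overstate the effect.** Treating all 29 completers per arm as intact pairs puts the unadjusted type I error at 2.9% and 2.0% for correlations of 0.2 and 0.3. With 30% dropout only about 20 pairs survive, and the error is nearer 3.7% and 2.8%.
- **A pair effect alone recovers less.** Even a best-case estimator that knows the correlation and keeps unpaired completers reaches about 53%, 56% and 60% power at correlations of 0.1, 0.2 and 0.3. This limits a pair-effect remedy. Covariate adjustment reaches 54%, 59% and 64%, because it also corrects for factor differences among patients who lost their partner.
- **Individual pairing is not stated.** The figures above assume it. The reasoning and the covariate remedy apply to frequency matching too, but the numbers are illustrative in that case.
- **Adjustment may be intended.** Table 3 lists socio-demographic characteristics under others/covariates, and the details could sit in a fuller plan. But the Statistical analysis section does name an unadjusted test. Its allowance for an equivalent most naturally means a non-parametric counterpart, which ignores the matching as well.

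**Conclusion.** The mismatch stands: the design matches on three factors and the stated between-group tests use none of them. The direction is certain if the factors predict KAB; the size is not. With 41 pairs, 30% independent dropout and d = 0.53, the power forgone is about 3, 8 and 13 points at R² of 0.1, 0.2 and 0.3, and nothing at R² = 0. The value of d comes from a before-after change in another study's fat and fibre behaviour score, so it is a planning figure only.

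This is an efficiency defect in the conservative direction. It should be corrected because the named test has only about 51% power at the expected number of completers and the correction costs almost nothing.

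**What to change.** State that the primary between-group comparison of KAB is a linear model (ANCOVA or mixed model) with age, sex and ethnicity as covariates. For binary outcomes, replace plain chi-square with logistic regression on the same factors. This works whether matching is by pair or by frequency, and it keeps patients whose partner drops out. Add a random effect for matched set only if individual sets are identifiable in the data. Do not substitute a plain paired t-test. State also which kind of matching was used.

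The cost is a change of wording and a few degrees of freedom, or about one point of power if the factors turn out to be unrelated to KAB (50% v 49%). No new data are needed, because the matching factors are known at allocation.

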## Background

Diabetes is a growing concern in Malaysia and in the world. The prevalence of diabetes in adults worldwide was estimated to rise 366 million in the year 2030 from 171 million in 2000 [1]. The prevalence of Type 2 Diabetes Mellitus (T2DM) in Malaysians above 30 years old was reported to be between 11% and 14% in 2006, and it is estimated to rise further [2]. T2DM accounts for a huge burden of morbidity and mortality through micro and macrovascular complications [3,4]. This has lead to an increasing demand on dietary and lifestyle modifications to delay the disease progression.

Web-based interventions have been successfully implemented in improving self-management of diabetes [5-8], physical activity [9,10] and weight management [11,12] in adults with T2DM. A web-based nutrition education for diabetes prevention study among young adults has shown significant reduction in dietary fat intake [13]. To date there is no published study focused solely on dietary behaviour change in adults with T2DM via a website-based system. Nevertheless, dietary modification has been incorporated as a component of multifactorial behavioural interventions in diabetes prevention and management [11,12,14].

The success of a web-based intervention relies heavily on the website log-in rates, usability, and personalisation. Content development in simplified local language improves the usability of the website [15], while regular reinforcement using reminder services such as e-mails and SMS increases the log-in rates [16]. The use of behavioural theories could assist the personalisation of web-based interventions. Transtheoretical Model (TTM) [17] is one of such behavioural model that has been recently used in web-based interventions, especially those focusing on improving dietary and lifestyle behaviours [10,18].

The study protocol for a randomised controlled trial (RCT) of a web-based dietary intervention for patients with T2DM in Malaysia is presented here. We hypothesised that the e-intervention group will show a greater improvement in dietary KAB than the control group. Secondly, we hypothesised that the web-based intervention to results in a better dietary practices, anthropometric measurements and blood biomarkers in the e-intervention group than the controls.

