#### Recruitment process

The eligibility screening, recruitment of study participants and data collections are conducted in the outpatient medical clinic of three urban hospitals in Malaysia. Diabetic nurses provide assistance in identifying potential study participants according to the eligibility criteria (Table 1). If the patients are found have potential to participate in the study, they complete the baseline questionnaire after giving a written informed consent. They are, however, excluded if the baseline dietary KAB score was more than 50%.

**Table 1 T1:** Eligibility criteria

Inclusion	Exclusion
Mentally sound men and women who are ≥ 18 years old. Literate with a fair command of English and/or Malay languages. Have access to the Internet at home, work or public place. Willing to access the study website at least once every fortnight. Have been confirmed of having HbA1c of ≥7.0%.	Pregnant, lactating or intend to become pregnant during the study period. Diagnosed with Type 1 Diabetes Mellitus (T1DM) or Gestational Diabetes Mellitus (GDM) Weighing more than 150% of the desired weight for height. Any pre-existing condition compromising the quality of life or ability to participate according to protocol. Have severe complications (chronic heart disease, cerebrovascular disease, diagnosed HIV/AIDS, cancer, emphysema, chronic liver or kidney disease) that would affect the subjects' ability to follow the tailored advice. Enrolled in other clinical studies. Having dietary KAB score more than 50% at baseline.

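### The repeated-measures ANOVA is directed at change within each arm, which does not test greater KAB improvement than control, and selection on baseline KAB makes within-arm p-values misleading

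*Protocol article*

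**What the plan says.** All references are to the protocol article.

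- **Hypothesis (Background):** "We hypothesised that the e-intervention group will show a greater improvement in dietary KAB than the control group". This compares the two arms.
- **Between-arm test (Statistical analysis):** an independent t-test or equivalent "is used to determine differences between the study groups for continuous variables". The text does not say which visit is compared, whether the variable is the follow-up score or the change, or whether baseline is adjusted for.
- **Longitudinal model (Statistical analysis):** "the ANOVA repeated measures model is applied to observe significant differences within the study groups". No group-by-time term is named.
- **Analysis set (Statistical analysis):** "The evaluation of the intervention is based on an intention-to-treat analysis".
- **Entry rule (Recruitment process; also Table 1):** "They are, however, excluded if the baseline dietary KAB score was more than 50" per cent. Patients complete the baseline questionnaire after consent and are then excluded on its score, so the screening value and the baseline value of the primary outcome are one measurement.

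**The concern.** The model that could carry the comparison of improvement over time is assigned to a different question. Change within the e-intervention arm mixes any effect of the website with everything else that moves the score between visits. Finding significance in one arm and not in the other is not a test of the difference between them.

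This trial is more exposed than most, because the primary outcome is also the selection variable. People admitted for a low score tend to score higher when measured again, whether or not they were treated. A significant rise within the e-intervention arm could therefore appear with no intervention effect and be read as benefit.

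A second, smaller matter is precision. Every participant has a baseline KAB score, and a between-arm test on follow-up scores that leaves it out gives up information already collected.

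**Working it through.** **1. Hypothesis against analysis.** The hypothesis concerns (change in e-intervention) minus (change in control). The ANOVA as described looks at each change separately. The t-test does compare arms. With randomised arms the expected baselines are equal, so a difference in follow-up means and a difference in mean changes estimate the same effect. The comparison therefore exists, but it is not specified as the primary KAB contrast.

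**2. The plan's own sample size.** The article states that "31 patients are needed in each group to detect this difference with a two-sided alpha of 0.05, a power of 80" per cent, using scores of 1.93 (SD 0.5) at baseline and 1.69 (SD 0.4) after intervention. The difference is 0.24.
- As a paired pre-post test with an assumed correlation of 0.5 (none is given): variance of change = 0.25 + 0.16 − 2 × 0.5 × 0.5 × 0.4 = 0.21, so SD = 0.458. The exact t calculation gives 31, as stated.
- As a two-arm comparison with pooled SD √((0.25 + 0.16)/2) = 0.453: the exact t calculation gives 57 per arm.

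So the stated 31 fits a within-arm calculation. The size of the trial is a separate matter. It is noted here only because it shows the same within-arm framing.

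**3. Expected rise with no effect.** The article gives no KAB mean, SD or retest correlation, so these are assumptions: normal scores, unselected mean μ of 45 to 55, SD 10, retest correlation r of 0.5 to 0.8. With a = (50 − μ)/10 and λ = φ(a)/Φ(a), the expected rise among patients admitted at 50 or below is (1 − r) × 10 × λ, the same in both arms.
- μ = 50, r = 0.7: λ = 0.399/0.5 = 0.798; rise = 0.3 × 7.98 = 2.4 points.
- μ = 55, r = 0.5: λ = 0.352/0.309 = 1.141; rise = 0.5 × 11.41 = 5.7 points.
- μ = 45, r = 0.8: λ = 0.352/0.691 = 0.509; rise = 0.2 × 5.09 = 1.0 point.

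**4. Simulated trials with no effect in either arm** (31 per arm, 4,000 trials per row). The within-arm test is a paired t-test, which is what a repeated-measures ANOVA reduces to with two visits. Within-arm results count as significant at p < 0.05 with a rise.

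| μ | r | Mean rise | Within-arm significant | e-intervention arm only | Between arms, follow-up score | Between arms, change score |
|---|---|---|---|---|---|---|
| 50 | 0.5 | 4.0 | 66% | 23% | 4.6% | 4.7% |
| 50 | 0.7 | 2.4 | 41% | 24% | 5.5% | 4.9% |
| 50 | 0.8 | 1.6 | 30% | 21% | 4.4% | 4.6% |
| 55 | 0.5 | 5.7 | 92% | 7% | 4.9% | 4.9% |
| 55 | 0.7 | 3.4 | 72% | 21% | 5.1% | 4.9% |
| 55 | 0.8 | 2.3 | 53% | 27% | 4.9% | 5.2% |

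Extending the grid down to μ = 45 lowers the within-arm figure to 14% (at r = 0.8). Over all scenarios the between-arm t-test rejected in 4.4 to 5.8% of trials, which is its nominal 5% apart from simulation error.

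**5. Precision gained by adjustment.** Relative to a t-test on follow-up scores, baseline adjustment removes a share of residual variance equal to the squared correlation among enrolled patients. Truncation at 50 lowers that correlation. At μ = 50 the baseline variance falls from 100 to 100 × (1 − 0.798²) = 36.3, and the share removed is 36.3r² / (36.3r² + 100(1 − r²)).
- r = 0.6: 13.1/(13.1 + 64) = 17%, against 36% without truncation.
- r = 0.7: 17.8/(17.8 + 51) = 26%, against 49% without truncation.

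Over the whole grid the share is about 8 to 46%.

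**The case against.** A reader might go further in three ways, and the article does not support any of them.

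- **That no planned analysis tests the hypothesis.** A between-arm test for continuous variables is planned. KAB is continuous, and after randomisation the comparison of follow-up scores is a valid test of the effect.
- **That this t-test ignores baseline.** The article does not say so. A t-test on change scores would use baseline and test improvement directly.
- **That regression to the mean will show as benefit.** It acts equally on both arms and cancels in the comparison between them, as the last two columns of the table show. It misleads only through within-arm results.

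It can also be said that the article nowhere makes within-arm significance the criterion of success. Its hypothesis is comparative, and the Discussion looks for a net gain. A condensed article may leave the visit, the form of the outcome and covariate adjustment to fuller documents. An unadjusted comparison in a randomised trial is not an error.

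These arguments stand as limits on the point. They do not remove it, because the purpose of the repeated-measures model is stated in the article and not merely left out, and the stated purpose is the wrong contrast for the hypothesis. The entry rule then makes any p-value from that model hard to interpret.

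HbA1c, with entry at 7.0% or more, may be affected similarly in the opposite direction. The article does not say whether the qualifying value is also the analysed baseline, so this is only a possibility.

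**Conclusion.** The point holds in a limited form. The repeated-measures ANOVA, as described, does not test the hypothesis. The between-arm t-test is valid but is not identified as the primary KAB contrast. With no intervention effect, the within-arm test would be significant in 14 to 92% of trials. That range rests on assumed values for the unselected mean, SD and retest correlation, and its width shows that the article cannot fix the size. The direction follows from the entry rule: some regression upward in both arms is expected whenever retest correlation is below 1.

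The planned between-arm comparison is not biased by this, so the trial can still answer its question. The danger is that within-arm results are read as efficacy. The precision argument for baseline adjustment is real but moderate, about 17 to 26% less residual variance at an unselected mean of 50 and r of 0.6 to 0.7. The unselected r² would overstate it.

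**What to change.** Reword the analysis section as follows.

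1. Make the primary KAB analysis one between-arm contrast adjusted for baseline KAB, reported with a 95% confidence interval. It can be ANCOVA at a named time point (6 or 12 months). It can also be a linear mixed model with group, visit, group-by-visit and baseline KAB, with the primary visit named.
2. Use the same form for the other continuous outcomes, each adjusted for its own baseline.
3. Report changes within each arm as description only, with no p-values and no claim of efficacy.

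The cost is a change of text before the analysis. Baseline KAB is already collected on everyone, so no extra data, visits or patients are needed.

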**Methods/Design:**

A minimum total sample of 82 Type 2 diabetics will be randomised, either to the control group, who will receive the standard diabetes care or the e-intervention group, who will participate in a 6-month web-based dietary intervention in addition to the standard care. The dietary recommendations are based on existing guidelines, but personalised according to the patients' Stages of Change (SOC). The participants will be followed up for 6 months post-intervention with data collection scheduled at baseline, 6-month and 12-month.

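### The intention-to-treat claim is paired with t-tests and repeated-measures ANOVA that use only observed or complete cases, and neither is specified to test the hypothesised difference in change

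*Protocol article*

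**What the plan says.** The relevant statements are in the Statistical analysis section, the sample size section and the Abstract of the protocol article.

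- **Principle.** "The evaluation of the intervention is based on an intention-to-treat analysis".
- **Between-group method.** An independent t-test or an equivalent "is used to determine differences between the study groups for continuous variables".
- **Repeated-measures method.** Because the trial measures participants repeatedly, "the ANOVA repeated measures model is applied to observe significant differences within the study groups".
- **Software.** SPSS 17.0 for all statistical analyses.
- **Visits.** The Abstract has "data collection scheduled at baseline, 6-month and 12-month".
- **Expected loss.** "Based on 30% attrition rate for one year, a minimum of 41 participants are required in each group".

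The Background hypothesises a larger gain in dietary KAB in the e-intervention arm than in the control arm. The article does not say how a missing visit is handled. It does not say that participants with a missing visit are excluded, and it does not say that their scores are imputed.

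**The concern.** Intention-to-treat means analysing everyone randomised, in the arm allocated. Classical repeated-measures ANOVA in SPSS deletes a participant entirely if any one of the repeated scores is missing. An independent t-test uses only those with a score at the visit tested. With three visits and a planned loss of 30%, neither method delivers the stated principle on its own.

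The stake is twofold. Scores that were collected would go unused in the ANOVA, in a trial with only 82 participants planned. Also, the main hypothesis concerns a difference between arms in change over time. The article assigns the only longitudinal model to change within the groups, and it does not say whether the t-test compares change from baseline or the score at a visit. No named model is specified to estimate the group-by-time effect.

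**Working it through.** **Inputs from the article.** 31 per group before attrition, 30% attrition over one year and 41 per group after it (sample size section); 82 in total and three visits (Abstract).

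**Inputs not in the article.** The way the two methods treat missing scores is a property of the methods. The share lost by month 6, called *a*, is not given, so I let it run from 0% to 30%. I assume that participants who are lost do not return, that loss is equal in both arms, and that nothing is imputed.

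**Step 1: the plan's own figure.** 31 × 1.30 = 40.3, rounded up to 41 per group, and 2 × 41 = 82. This reproduces the stated numbers.

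**Step 2: participants in the repeated-measures ANOVA.** Only those with all three visits enter.
- Per arm: 41 × (1 − 0.30) = 28.7, about 29.
- In total: 82 × 0.70 = 57.4, about 57.
- Left out: 82 − 57.4 = 24.6, about 25 of those randomised.

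The 28.7 per arm is below the 31 that the plan says it needs, because the allowance multiplies by 1.30. Dividing by 0.70 would give 31 / 0.70 = 44.3, so 45. That is a separate matter.

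**Step 3: participants in the t-tests.** At 12 months the t-test has 82 × 0.70 = 57.4. At 6 months it has 82 × (1 − *a*):

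| Lost by month 6 (assumed) | 6-month t-test | ANOVA | In the 6-month t-test but not in the ANOVA |
|---|---|---|---|
| 0% | 82.0 | 57.4 | 24.6 |
| 10% | 73.8 | 57.4 | 16.4 |
| 15% | 69.7 | 57.4 | 12.3 |
| 20% | 65.6 | 57.4 | 8.2 |
| 30% | 57.4 | 57.4 | 0.0 |

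Unless all loss falls before month 6, the 6-month t-test and the ANOVA describe different participants.

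**Step 4: hypothesis against methods.** The hypothesis is a between-arm difference in improvement. The ANOVA is assigned to change within groups. A significant change in one arm and a non-significant change in the other is not a test of the difference between them. A t-test on change from baseline would address the hypothesis at one visit, but the article does not say that the t-test is on change.

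**Step 5: what a likelihood-based model keeps.** A baseline KAB score decides eligibility (Recruitment process and Table 1), so every randomised participant should have at least one KAB score. All 82 would then be in the analysis set. The model does not replace missing 12-month scores; it uses the earlier scores of those participants instead of discarding them.

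**The case against.** The strongest objection is that the ANOVA does not carry the treatment comparison. The text gives that to the t-test, which at 6 months keeps everyone who has a 6-month score. This stands. A reader might infer that someone seen at 6 months and lost by 12 months would drop out of the 6-month comparison of the arms. The article does not support that, because it does not specify a between-group ANOVA.

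The second objection is that intention-to-treat and repeated-measures ANOVA are compatible if missing scores are imputed. A condensed article may leave that to a full protocol or analysis plan that is not shown. This also stands, so the article cannot be said to commit itself to a completers-only evaluation. The point does not rest on silence about imputation, however. It rests on three things the article does state: the principle, methods that need observed or complete data, and an expected loss of 30%.

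A reader might also infer that the treatment effect would be overstated because unresponsive e-intervention participants leave more often. The Discussion says that the programme's success depends on log-in rates. It does not say that people who do not log in miss assessments, and these are done in the clinic by trained enumerators. Any figure for such a bias would need a dropout pattern that the article does not give.

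**Conclusion.** The point holds in this limited form. The intention-to-treat claim and the named methods do not fit together at the plan's own attrition unless missing scores are imputed. Without imputation, the ANOVA would use about 29 of 41 per arm (57 of 82), and the 12-month t-test about the same number. The 6-month t-test would use between 57 and 82, depending on when the loss occurs. The analyses would generally rest on different participant sets, and neither is specified to test the hypothesised greater improvement against control.

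The counts rest on the stated 30%, equal loss in both arms and no return after loss. Participants who miss month 6 but attend month 12 would lower the ANOVA count further. No direction or size of bias is claimed.

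**What to change.** For the KAB score and the other continuous outcomes, replace both the t-tests and the repeated-measures ANOVA with one likelihood-based linear mixed model, fitted with the MIXED procedure of SPSS:

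- responses: the baseline, 6-month and 12-month scores;
- fixed effects: group, visit and group-by-visit;
- covariance across visits: unstructured;
- analysis set: every randomised participant with any score, in the arm allocated, with no requirement for a post-baseline score;
- treatment effect: the group-by-visit contrasts, that is, the difference between arms in change from baseline at 6 and at 12 months.

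Requiring a post-baseline score would itself narrow the intention-to-treat set, so that condition should not be added.

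The cost is a change of wording in the Statistical analysis section and slightly more analysis work. Recruitment, visits and data collection do not change. The model relies on scores being missing at random given the observed data, and the text should say so.
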